**5.4.3 Parameters to be Monitored**

The following progress will be monitored throughout the course of the research to ensure the safety of subjects as well as the integrity and confidentiality of their data.

- An evaluation of the progress of the research study, including subject recruitment and retention, and an assessment of the timeliness and quality of the data.
- A review of collected data (including adverse events, unanticipated problems, and subject withdrawals) to determine whether there is a change to the anticipated benefit-to-risk assessment of study participation and whether the study should continue as originally designed, should be changed, or should be terminated.
- An assessment of external factors or relevant information (eg. Pertinent scientific literature reports or therapeutic development, results of related studies) that may have an impact on the safety and study participants or the ethics of the research study.
- A review of study procedures designed to protect the privacy of the research subjects and the confidentiality of their research data.

The National Cancer Institute Common Toxicity Criteria Scale (Appendix 3) will be used to define grades (severity) of adverse events and toxicities. Previous experience with rituximab has demonstrated common side effects that may occur during treatment. An adverse event is any untoward medical occurrence in a participant who received study drug, regardless of its relationship to the study drug. Toxicity is an adverse event with a direct relationship to the study drug. All toxicities are adverse events, but not all adverse events are toxicities. This is a determination made by the study investigator. The study investigators will classify adverse events as “definitely or most likely,” “possibly,” or “very unlikely” due to the study drug. Toxicity will be defined as an adverse event that is definitely, most likely, or possibly caused by the study drug.

The severity of adverse changes in physical signs or symptoms will be classified as follows:

- Grade 1 (Mild): asymptomatic or mild symptoms; clinical or diagnostic observation only; intervention not indicated.
- Grade 2 (Moderate): minimal, local or noninvasive intervention indicated; limiting age-appreciate instrumental ADL (Activities of Daily Living).
- Grade 3 (Severe): medically significant but not immediately life-threatening; hospitalization or prolongation of hospitalization indicated; disabling; limiting self care ADL.
- Grade 4 (Life-threatening): consequences; urgent intervention indicated.
- Grade 5 (Death): event is a direct cause of death.

**5.4.4 Frequency of Monitoring**

The principal investigator will review subject safety data as it generated. The principal investigator, co-principle investigators, and the research staff will meet on a two week interval to re-evaluate study goals, subject recruitment, data coding and retention, documentation and identification of adverse events, complaints and confidentiality of subjects. There will be an evaluation of the progress of the research study, including assessments of data quality, time lines, participant recruitment, accrual, and retention. The principal investigator will also review the outcome and adverse event data to determine whether there is any change to the anticipated benefit-to-risk ratio of study participation and whether the study should continue as originally designed or should it be re-evaluated and changed.

The DSMB will also be expected to meet as needed, but not less than, every six months to provide an overall summary status report to the regulatory agencies.

**5.4.5 Reportable Adverse Events**

For this study, a serious adverse event is any untoward clinical event that is thought by the investigator to be study-related, that is also:

1. Fatal or immediately life threatening

2. Permanently disabling, or severely incapacitating.

3. Requires, or prolongs inpatient hospitalization.

4. Important medical events that may not result in death, be life threatening, or require hospitalization may be considered serious adverse events when, based upon appropriate medical judgment, they may jeopardize the patient, or subject, and may require medical, or surgical intervention to prevent one of the serious outcomes listed above.

If clinically important and unexpected adverse experiences, or clinically important study-related adverse experiences occur, they will be recorded on the adverse event case report form.

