Plasma exchange (PEX) will consist of 1.5x estimated plasma volume exchanges for 3 successive days (0, 1,2) and then, after a one day interval to enable equilibration of autoantibodies sequestered in tissues, two more daily treatments on days 4 and 5. It is anticipated that fluid replacement with 5% albumin:normal saline (3:1 ratio), with a net fluid balance of 95-100%, will be possible in nearly all patients for the first two treatments. In the event a subject’s INR is >1.5 at the initiation of a PEX treatment, as may occur on the third or later treatment, the albumin:saline replacement will be partially supplanted with fresh frozen plasma (FFP) (anticipated to be <10 U/treatment) to maintain INR <1.6. The dialysis catheter will be removed after completion of the 5th and final PEX.

Rituximab: One gm i.v. will be administered on day 5 (after completion of the last PEX) and day 13. This regimen is adopted from the protocol of a recent large myositis trial at UPMC and other sites (NIHNO1 AR42273) and was well tolerated. Subjects will be treated with acetaminophen, antihistamines and methylprednisolone 100 mg i.v. prior to administration of rituximab to obviate reactions.75

The study design and flowchart is outlined in the table below (Appendix 1).

| Combined Treatment | **Days on Interventions** | | | | | | | | | |
| --- | --- | --- | --- | --- | --- | --- | --- | --- | --- | --- |
| **0** | **1** | **2** | **3** | **4** | **5** | **6-12** | **13** | **14-28** | **> 28** |
| Steroids | 1 gm /day, IV | 40 mg/day, IV  or oral Prednisone equivalent | | | | 100 mg  /day, IV | 40 mg/day, IV  or oral Prednisone equivalent | 100 mg  /day, IV | 20 mg/day, IV  or oral Prednisone equivalent | Tapering thereafter at the discretion of the treating physician |
| Plasma Exchange | 1.5x estimated plasma volume exchange/day | | | NA | 1.5x estimated plasma volume exchange/day | | NA | | | |
| Rituximab | NA | | | | | 1gm  /day, IV | NA | 1 gm  /day, IV | NA | |

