**2.3 STUDY ENDPOINTS**

**2.3.1. The Primary End-Points**

The primary outcome measures for this study are the feasibility and safety of the regimen in patients with IPF exacerbations. Safety will be assessed by monitoring three variables of cardiopulmonary function:

- Respiratory deterioration defined as PaO2 on days 0, 3, 5, 7, 14, 28 (if still hospitalized) while breathing 100% FiO2 for >20 minutes by either endotracheal tube (ETT) or nonrebreathing face mask if not intubated (face masks and O2 delivery systems for nonintubated patients will be standardized).
- Hemodynamic deterioration defined as need for initiation of vasopressor agents, inotropes, or intravenous diuretics.

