**5.4.2 Data Safety Monitoring Plan**

Assuring patient safety is an essential component of this protocol. The study Principal Investigator has primary responsibility for the oversight of the data and safety monitoring. The study investigators will evaluate all adverse events. All subjects who have AEs, whether considered associated with the use of the study medication or not, must be monitored to determine the outcome. The clinical course of the AE will be followed up according to accepted standards of medical practice, even after the end of the period of observation, until a satisfactory explanation is found or the Principal Investigator considers it medically justifiable to terminate follow-up.

The study coordinators must view patient records for possible adverse events until 72 hours after the last dose of study drug. All untoward medical occurrences observed in subjects receiving the study drug will be recorded on the participants’ adverse event case report forms (CRF) by the study coordinator under the supervision of the principal investigator. The CRFs will then be reviewed for completeness and internal consistency. Subsequently, the CRFs will be recorded on an electronic password-guarded study database. In addition to internal safeguards built into a computerized system, external safeguards will be put in place to ensure that access to the computerized system and to the data is restricted to authorized personnel. Training conducted by qualified individuals on a continuing basis will be provided to individuals in the specific operations with regard to computerized systems that they are to perform during the course of the study.

The PI, will work with the reporting investigators to prepare a detailed written summary of serious, unexpected, and treatment related adverse events, and will compare, and contrast the event with prior events. The detailed written summary will be provided to the local DSMB and the IRB.

In addition, the DSMB Report addressed the following information will be submitted to the IRB at the time of continuing review annually or more often as required:

- A list of the research personnel who participated in the data and safety monitoring.
- The frequency of monitoring that took place during the renewal intervals and/or the dates that data and safety monitoring was conducted.

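### The SAE definition requires investigator-judged relatedness and record review stops 72 hours after the last dose, so the SAE tally and late adverse-event capture can be incomplete

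*Protocol*

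**What the plan says.** The protocol's safety rules are spread over several sections.

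- **Definition of an adverse event (5.4.3).** "An adverse event is any untoward medical occurrence in a participant who received study drug, regardless of its relationship to the study drug".
- **Definition of a serious adverse event (5.4.5).** "a serious adverse event is any untoward clinical event that is thought by the investigator to be study-related", and that also meets one of four seriousness criteria.
- **What goes on the case report form.** Section 5.4.2: "All untoward medical occurrences observed in subjects receiving the study drug will be recorded". Section 5.4.5: "If clinically important and unexpected adverse experiences, or clinically important study-related adverse experiences occur, they will be recorded".
- **How long records are searched (5.4.2).** "The study coordinators must view patient records for possible adverse events until 72 hours after the last dose of study drug". The protocol does not define study drug.
- **How long adverse events are collected (2.2.2).** They are documented at visits on days 0, 7, 14 and 28 (or discharge), and again at the day-60 contact.
- **What is analysed (2.4.2).** A treatment-emergent event is any new or worsened event reported after enrollment, with no relatedness condition and no 72-hour limit.
- **Primary safety (2.3.1).** "Safety will be assessed by monitoring three variables of cardiopulmonary function". The two listed are PaO2 on set days to day 28 while the subject is in hospital, and the start of vasopressors, inotropes or intravenous diuretics.

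**The concern.** Seriousness describes the outcome of an event; relatedness is an opinion about its cause. Section 5.4.5 makes the first depend on the second. The trial is open-label with one arm, so the person judging the cause knows that the treatment was given, and no concurrent group exists to show misattribution. Respiratory failure and death are also the expected course of the disease: section 1.3 puts hospital mortality at about 50%. Some harms in section 5.1.2, such as infusion reactions or a pneumothorax from the catheter, can often be attributed by timing or mechanism. Respiratory decline or infection is much harder to assign.

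The short record review adds to this. Section 5.1.2 lists infections and hepatitis B reactivation among the rituximab risks, and nothing in the text confines them to three days after a dose. At stake are two things that a small safety trial should hand on to the larger trial foreseen in section 2.4.1: a complete count of serious events, and complete adverse-event data after the treatment phase.

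**Working it through.** The protocol states no figure for this point, so there is none to reproduce. The check compares the rules and then works out the review window.

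**1. A fatal respiratory failure that the investigator attributes to IPF, followed through the rules**

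| Rule | Is the event included? |
|---|---|
| Adverse event, 5.4.3 | Yes |
| CRF rule, 5.4.2 | Yes, if observed |
| CRF sentence, 5.4.5 | Not required if judged both expected and unrelated |
| SAE, 5.4.5 | No |
| Expedited report, 5.4.6 | No (needs association with study drug or procedures, and unexpectedness) |
| Treatment-emergent event, 2.4.2 | Yes, if reported |
| 60-day survival endpoint, 2.3.2 | Counted as a death unless the subject was transplanted first |

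The death is known to the trial but is missing from the SAE tally. Whether it reaches the adverse-event form depends on which recording rule staff follow.

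**2. End of record review**

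Inputs: rituximab "One gm i.v. will be administered on day 5 (after completion of the last PEX) and day 13" (2.2.1); scheduled steroid dosing to day 28, then a discretionary taper (2.2.1); review to 72 hours (3 days) after the last dose (5.4.2); follow-up to day 60 (2.2.2).

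End of review = day of last dose + 3. Share outside review = (60 − end of review) / 60.

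| Reading of study drug | Last dose | Review ends | Days outside | Share |
|---|---|---|---|---|
| Rituximab, both doses | day 13 | 13 + 3 = day 16 | 60 − 16 = 44 | 44/60 = 73% |
| Rituximab, day-5 dose only | day 5 | 5 + 3 = day 8 | 60 − 8 = 52 | 52/60 = 87% |
| Corticosteroids count, last dose on day 28 | day 28 | 28 + 3 = day 31 | 60 − 31 = 29 | 29/60 = 48% |

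If the taper after day 28 also counts, review ends later than day 31 and the last share falls.

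**3. What is left after review ends on day 16**

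The visit on day 28 is 12 days later (28 − 16), or the last visit is at discharge if that comes first. After that comes the day-60 contact. A subject discharged early has no scheduled contact between discharge and day 60. For a subject who dies after discharge, the day-60 contact can establish the death, but the protocol names no source for the details of the events that led to it.

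**4. Scale in the SAE tally**

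With 10 subjects, one subject whose serious event is left out changes the proportion by 1/10 = 10 percentage points. As an illustration, section 2.4.1 uses 50% survival for controls and 90% as the hoped-for result. These would give 10 × 0.5 = 5 and 10 × 0.1 = 1 deaths. If every death were attributed to IPF, 1 to 5 deaths would be absent from the tally. That is a worst case for the label, not an estimate of how many would be misattributed.

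**The case against.** A reader might infer that the primary safety outcome is under-counted. The documents do not support that. The two variables listed in section 2.3.1 carry no relatedness condition, and PaO2 has its own measurement days. Section 2.3.1 gives no end date or method of ascertainment for hemodynamic deterioration, so late events could in principle be missed, but nothing says that they are found through adverse-event record review.

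A reader might also infer that deaths are lost. They are not: 60-day survival or survival to transplantation is the secondary endpoint whatever the attribution, and the day-60 contact serves to establish survival.

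Three further defences deserve weight.

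- **No stated analysis uses the SAE count.** The only adverse-event analysis uses any new event after enrollment. This is correct and limits the consequence. That definition can include only what was reported, however, so it does not repair thin capture.
- **The 73% is not a capture gap.** It rests on one reading of an undefined term, and other routes remain open: visits, daily inpatient progress notes, the day-60 contact and two-weekly team meetings. This stands. The figure describes the reach of record review only.
- **The recording sentence in 5.4.5 does not say that only those events are recorded.** It can be read together with 5.4.2. This also stands: the sentence is loose and is not a prohibition.

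None of this answers the SAE definition itself, which excludes unrelated events on its face, or the mismatch between a 72-hour search and a 60-day collection period.

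**Conclusion.** The point holds for the SAE tally and for late adverse-event capture. As written, fatal or life-threatening events judged unrelated are not SAEs, and the two recording rules invite different practice. Record review covers 16 of 60 days if study drug means rituximab and both doses are given; under the other readings it ends on day 8, or on day 31 or later.

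The listed primary safety variables and the survival endpoint are not affected by the SAE definition. Section 2.3.1 announces three variables and lists two, so this statement covers only those two. The documents give no basis for estimating how many events would be missed.

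This should be fixed because safety is a stated primary purpose of an open-label, one-arm trial with high mortality and the correction is cheap. It does not invalidate the primary assessment.

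**What to change.** 1. **5.4.5, definition.** Delete the condition that the investigator must consider the event study-related. An SAE is then any adverse event that meets criteria 1 to 4, with causality recorded as a separate item. Expedited reporting in 5.4.6 may stay limited to associated, unexpected events.
2. **5.4.5, recording.** Remove the narrower CRF sentence and keep the 5.4.2 rule, under which all untoward occurrences are recorded, as the only one.
3. **5.4.2, record review.** Extend coordinator review from 72 hours after the last dose to day 60 or death. This matches section 2.2.2, and the end of review no longer depends on what study drug means.

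The cost is protocol wording and chart review to day 60 for 10 subjects. The reported SAE count will be higher, since it will include events of the disease itself; the separate causality item lets a reader tell them apart.

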**5.4.6 Adverse Events Reporting Timeline**

Life-threatening or fatal unexpected adverse events associated with the use of the study drug or procedures must be reported to the DSMB and the IRB within 24 hours of discovery of the incident with subsequent follow-up submission of a detailed written report.

Serious (but not fatal or life-threatening) and unexpected adverse events associated with the use of the study drug or procedures must be reported to the DSMB and the IRB within 5 working days with subsequent follow-up submission of a detailed written report.

A summary report of the DSMB’s findings will be prepared and submitted to the regulatory agencies.

**5.5 RISKS MANAGEMENT PROCEDURES**

**5.5.1 Protection Against Risks**

General Risks of Study Protocol and Procedures

All research interventions/activities will be conducted in private patient care areas. The collection of sensitive information about subjects is limited to the amount necessary to achieve the aims of the research, so that no unneeded sensitive information is being collected.

All demographic and clinical information about the subject will be stored on an electronic password-guarded study database under the supervision of the PIs for this protocol. The data will be stripped of individual identifiers and stored anonymously with a subject number. Information linking subject identifiers with the coded subject number will be stored under password protection on computers in locked areas, with access only to the database manager. Maintaining records in locked files in locked offices will protect confidentiality of subjects. All staff will sign confidentiality statements. Access to the database will be limited to the data manager and staff under the supervision of the PIs.

Specimens will be stripped of subject identifiers and stored according to a similar coding protocol as described above. These specimens will be stored safely in the custody of the Principal Investigator responsible for the individual assays. These Investigators will limit future access to any remaining sample to only those investigators with prior IRB approval for their studies.

All staff involved in this study are properly credentialed and instructed in the areas of testing, confidentiality, and safety.

The PIs will retain the data for the entire period of this study. The investigators may continue to use and disclose subjects de-identified information for the purpose of this study for a minimum of six years after final reporting or publication of the study. If the subject and/or legal representative decide to withdraw or be withdrawn from study participation, they may request that the study data and samples be destroyed.

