**2.4 STATISTICAL APPROACH**

**2.4.1 Sample Size and Power**

This is an exploratory observational trial to demonstrate feasibility and the statistical power analysis for the sample size is not appropriate. The sample size of 10 for this clinical trial is based upon: 1) exposing a minimum number of patients to potential risks of the experimental treatment while still obtaining useful information; 2) the intent to collect detailed and comprehensive data in each subject to provide comprehensive information relevant for design of a future larger trial, and also provide adequate specimens for the Ancillary Studies. This is an exploratory Phase I/II clinical trial focused on establishing proof-of-concept, and providing access to a novel treatment regimen in patients with a very high risk of hospital mortality.

Given the nature of this initial, exploratory and uncontrolled clinical trial, definitive power calculations are speculative. Nonetheless, high efficacy of the experimental treatment (as we anticipate) could produce evidence of same, given the usual high mortality of historical control patients. We are planning a study with 10 experimental subjects and 100 historical control subjects. A conservative estimate of survival among historical controls is 50%. If our treatment results in 90% survival, we will be able to reject the null hypothesis that the failure rates for experimental and control subjects are equal with probability (power) 0.6.

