**4.2 INFORMED CONSENT PROCEDURES**

The consent process will begin via one of two possible pathways:

1) Referral of the prospective participant to the investigators/research coordinator by a physician who has knowledge of the proposed research, and obtains patient/surrogate consent for the research team to approach the patient/surrogate.

2) Individuals who have provided signed IRB-approved HIPPA compliant consent for participation in clinical trial research registries.

Prior to performing any of the study procedures the subjects must provide informed consent. The information about this study will be given to subjects in language understandable to subjects. Only physician investigators will present the study to the potential subjects. The physician investigator will verbally present a general outline of the research plan, including inclusion and exclusion criteria, to the prospective participant. The consent form, outlining the design of the study, will include the risks and benefits of participating, and will be reviewed and the investigator will answer any questions. Prospective participants may take as much time as required to make an informed decision. Written informed consent will be obtained from each participant prior to performing any research study procedures.

In addition, older potential study participants whose competency to consent is in question will be tested for sufficient comprehension and recall of the information presented. Prospective subjects who do not remember the important facts about participation in the research study after repeated testing will not be included in the study. The investigators will also assess whether a participant understands experimental procedures over time, including assessment throughout the full duration of participation in the study.

Proxy consent:Given the nature of the study population, which frequently requires mechanical ventilation with sedation, surrogate consent, will occur in a proportion of the study population. This will remain a valid consent until the patient is fully alert, and aware, and can provide a second consent to continue participation in the study.

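### A withdrawing subject or representative may ask for study data to be destroyed, with no exception for adverse events or vital status already recorded, so the safety and 60-day survival results can be biased

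*Protocol*

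**What the plan says.** Section 5.5.1 (Protection Against Risks) sets out what happens on withdrawal: should a subject, or whoever legally acts for the subject, "decide to withdraw or be withdrawn from study participation, they may request that the study data and samples be destroyed". It sets no time limit, makes no exception for outcome or safety data already in the database, and does not say how such a subject is counted. Two sentences earlier the same paragraph says "The PIs will retain the data for the entire period of this study".

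Three other places bear on this:

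- Section 5.4.2 (Data Safety Monitoring Plan): "All subjects who have AEs, whether considered associated with the use of the study medication or not, must be monitored to determine the outcome".
- Section 4.2 (Informed Consent Procedures), on surrogate consent: "This will remain a valid consent until the patient is fully alert, and aware, and can provide a second consent to continue participation".
- Section 5.4.6 (Adverse Events Reporting Timeline): unexpected fatal or life-threatening events associated with study drug or procedures go to the DSMB and IRB within 24 hours. Other serious unexpected associated events go within 5 working days.

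Safety is a primary outcome (2.3.1). Survival to 60 days or to transplantation, compared with historical controls, is the secondary outcome (2.3.2).

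**The concern.** This is a rule that the protocol states, not a detail left to an analysis plan, and no later plan can analyse records that have been destroyed. The protocol gives no ground on which investigators could refuse or limit a request, so each would be settled case by case by people who know how the subject fared.

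The trial is open-label and ventilated subjects may be enrolled by surrogate. A representative can therefore withdraw a subject knowing that the course has been bad. A subject who has recovered can also withdraw and make the same request. In both cases the loss may be linked to outcome. With 10 subjects, one lost record changes both the numerator and the denominator of every proportion reported, including the adverse event percentages and the survival comparison.

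**Working it through.** **Inputs.** Section 2.4.1 gives the group sizes ("We are planning a study with 10 experimental subjects and 100 historical control subjects"), the control rate ("A conservative estimate of survival among historical controls is 50" per cent), the treated rate ("If our treatment results in 90% survival") and the power ("are equal with probability (power) 0.6"). Alpha, sidedness and the test for survival are not stated. I assume a two-sided Fisher exact test at 0.05. The number of destroyed records is also an assumption: 0, 1 or 2.

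**The plan's own figure.** For 90% against 50% with 10 and 100 subjects, the two-sided normal approximation with continuity correction uses:

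- pooled rate (9 + 50)/110 = 0.536
- null standard error √(0.536 × 0.464 × 0.11) = 0.165
- alternative standard error √(0.009 + 0.0025) = 0.107
- continuity correction 0.5 × (0.1 + 0.01) = 0.055

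Power = Φ[(0.4 − 0.055 − 1.96 × 0.165)/0.107] ≈ 0.577. Exact enumeration with the Yates-corrected chi-square gives 0.628. Both round to 0.6, so the stated power is not challenged. Other methods give more (Fisher two-sided 0.746, uncorrected chi-square 0.779). Nothing below depends on this figure.

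**Effect of lost records on the survival comparison.** Fix the margins and sum all hypergeometric probabilities no larger than that of the observed table, with controls at 50/100.

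- 8/10: 0.00034 + 0.00455 + 0.02652 + 0.05420 + 0.01181 + 0.00111 = 0.099
- 8/9: 0.00071 + 0.00866 + 0.02293 + 0.00250 = 0.035

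| Records destroyed | Observed | Rate | p |
| --- | --- | --- | --- |
| none | 8/10 | 80% | 0.099 |
| one failure | 8/9 | 89% | 0.035 |
| two failures | 8/8 | 100% | 0.007 |
| one success | 7/9 | 78% | 0.17 |
| two successes | 6/8 | 75% | 0.27 |

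At the plan's hoped-for 90%, the result is below 0.05 with or without the loss: 9/10 gives p = 0.019 and 9/9 gives p = 0.0035.

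**Long-run effect if only deaths are lost.** Suppose true survival is 50% in both groups and up to k death records are always destroyed. Expected observed survival is:

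- k = 0: 50.0%
- k = 1: (5 − 10/1024)/9 + 1/1024 = 55.5%
- k = 2: (5 − 100/1024)/8 + 11/1024 = 62.4%

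The chance of a significant result favouring treatment is 1.9%, 4.6% and 8.3% respectively. This is a one-directional worst case, not a forecast.

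**Safety.** One event in 10 (10%) becomes 0 in 9 (0%) if that subject's record is destroyed.

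**Which events are exposed.** Section 5.4.6 puts serious, unexpected, associated events into reports held outside the study database. Expected events, events judged not associated, non-serious events and deaths put down to IPF itself have no such expedited report. Those IPF deaths are failures on the secondary outcome unless they follow a transplant or day 60.

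**The case against.** The case on the other side is substantial.

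- **It is a right to request.** The text does not say that every request must be granted in full. Bias needs requests to occur, to be granted and to be related to outcome. The protocol gives no rate, and exclusion criterion 12 (3.3) keeps out those unwilling to complete 60 days of surveillance. This stands: the results can be biased, and nothing shows that they will be.
- **The DSMB and the halting rule.** A reader might infer that destruction hides events from the DSMB and from the stopping rule in 5.4.2. The documents largely do not support that. The rule concerns unexpected fatal or life-threatening events attributed to the study drug, and 5.4.6 sends these to the DSMB and IRB within 24 hours. A later request does not undo those reports.
- **Adverse event follow-up.** A reader might infer a flat contradiction with 5.4.2. That text concerns clinical follow-up of the event under accepted medical practice, not retention of a withdrawn subject's research data. The real tension is with the retention sentence inside 5.5.1.
- **Second consent.** A reader might infer that declining second consent removes recovered subjects. Section 4.2 makes it a consent to continue; refusal does not itself destroy data. Successes are lost only if a separate request follows under 5.5.1.
- **Timing.** If a subject is withdrawn before death, the missing outcome comes from the withdrawal, not from the destruction clause. The 8/10 to 8/9 case needs a request after failure is known, which the text neither describes nor excludes.
- **Other sources.** Clinical data come from medical records (2.2.2), which survive. The protocol does not, however, say that they may be re-extracted after study data are destroyed. The consent form is not at hand and may already limit the clause.

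**Conclusion.** The point holds in a limited form. Section 5.5.1 allows a request to destroy recorded study data, does not protect adverse events or vital status, and is not reconciled with the retention sentence beside it. Followed as written, it permits outcome-related loss of records affecting a primary and a secondary outcome. The direction is not fixed: losing failures flatters the treatment and losing recovered subjects does the opposite.

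The size depends on an unknown number of requests. One destroyed failure record can be enough to move the survival comparison across 0.05, under the assumed test and an assumed 8/10 result. At 9/10 it would not change that conclusion. The exposure is mainly expected or non-associated events and deaths attributed to IPF.

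**What to change.** In section 5.5.1 and the consent form:

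1. Limit destruction requests to stored samples and to future research use of data and samples.
2. State that data recorded up to withdrawal, including adverse events and vital status, are kept and analysed. This also settles the conflict with the retention sentence.
3. State that all enrolled subjects are reported in the denominator, including any who withdraw or decline second consent.

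This needs a short protocol and consent-form amendment, with no extra visits or staff. Its small downside is that a withdrawing subject can no longer have already recorded data erased. That changes what participants are offered, so it needs IRB agreement. The change does not recover outcomes that occur after withdrawal; it only stops recorded ones from being lost.
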